### Randomisation and service allocation

#### Sequence generation and allocation concealment

A computerized system will be used to generate a randomization list. The randomization will be stratified by health centre catchment area. Within each health centre catchment area, randomization will be organized with permuted blocks of random size so that an equal number will be randomized to the new intervention arm and to the active control arm. From the randomization list, labelled and sealed envelopes will be prepared containing cards with intervention allocation. The sealed envelopes will be handed over to independent clinicians working in Butajira hospital and will be kept in a secure place.

#### Intervention allocation

Upon completion of the baseline assessment, participants will be accompanied to Butajira hospital. In a fully private location, the independent clinician will open the next sequential envelope for the health centre catchment area where the person resides and inform the participant of the service to which they have been allocated (that is, psychiatric nurse-led care or care from the health centre staff).

### Masking

Outcome assessors and trial investigators will be masked to the intervention allocation of participants, but it is not possible for trial participants and clinicians involved in delivering the intervention service to be masked. To minimise the possibility of unmasking of outcome assessors, 1) outcome assessments will be carried out by project-employed mental health professionals and lay interviewers in a location that is independent of and geographically separated from the health service; 2) the outcome assessors will not work in the trial districts; 3) when patients and caregivers are registered for their follow-up assessments, they will be instructed not to tell the interviewer where they are receiving mental health care; 4) selected trial clinical assessments will be observed by non-project psychiatrists to ensure that ratings are being conducted without bias; and 5) at the end of each follow-up assessment, the assessor will be asked whether they have become unmasked to patient allocation group during the course of the assessment. This information will be used to conduct a sensitivity analysis to investigate any evidence of bias. Data analysis for the primary outcome will be carried out by an independent organization, and those involved in data analysis will be masked to the intervention status of the participant.

### Interventions

#### Intervention arm

The intervention is a task sharing model of mental health care for people with SMD integrated into PHC, as recommended by the WHO in the mental health Gap Action Programme (mhGAP) [21] and endorsed by the Ethiopian Federal Ministry of Health [16]. Adaptation of the task-sharing model for the study setting was informed by extensive formative work and community consultation in the study site [40] and from findings arising from a sister project implementing integrated mental health care in a neighbouring district [43, 44].

In the TaSCS intervention, PHC-based health centre nurses and health officers will be trained to deliver the mhGAP packages of mental health care, supported by community-based health extension workers. The training and supervision requirements are summarised in Table 1. As all trial participants have an existing care plan used by project psychiatric unit staff, this will be transferred to PHC when a patient has been randomised to a PHC site. A minimum of monthly, facility-based follow-ups will be stipulated during the initial phase, and thereafter, 3-monthly follow-ups, although contacts can be more frequent depending on patient need. The current outreach by project workers will be replaced by outreach by health extension workers, who are required to make house-to-house visits every 3 months, as part of their health promotion and illness prevention responsibilities. Psychiatric nurse-led mental health support will be provided to the PHC health officers and nurses through (1) supervision including case reviews, discussion of difficult cases, developing supportive relationships with the primary health care provider and trouble-shooting; (2) emergency consultation with project psychiatric nurses; and (3) referral for a second opinion or for a period of follow-up by the specialist team in Butajira psychiatric unit, as per mhGAP guidelines. Psychiatric nurses can in turn consult project psychiatrists. The roles of the PHC workers in the task shared model are summarised in Additional file 2.

**Table 1 Tab1:** Task sharing intervention for the Task Sharing for the Care of Severe Mental Disorders in a Low-income Country (TaSCS) trial

Recipients	Intervention	
	Training	Ongoing support and structures
Health centre nurses and health officers	9 days of training in mhGAP-IG packages (4 days of base course + 5 days of on-the-job training)	Phase I: Support and supervision by project psychiatric nurse tapering down from weekly to bi-weekly
	Delivered by project psychiatric nurse supported by project psychiatrist	Phase 2 onwards: Monthly support and supervision by project psychiatric nurse
	Pre-study run-in phase: on-the-job training with patients with SMD who volunteer for treatment in PHC, delivered by project psychiatric nurse	Supervision sessions will include discussion of all cases presenting with suicidal ideation or a psychiatric emergency, discussion of complex cases, developing supportive relationships with the general health care provider and trouble-shooting.
	1-day refresher training at 6 and 12 months	Emergency consultation with project psychiatric nurse
		Referral for specialist review at Butajira psychiatric unit
		Register of appointment times for persons with Severe Mental Disorder needing ongoing care
Health extension workers	2-day training course based on Ministry of Health training materials^*^.	Monthly supervision by health centre-based supervisor
	Delivered by project psychiatrist	Consultation with health centre supervisors
District health office and community stakeholders	Stakeholder workshop facilitated by project psychiatrists	Regular meetings of the trial advisory board and one-to-one liaison of project psychiatric nurse with district health office heads

* http://www.open.edu/openlearnworks/course/view.php?id=19%3f

#### Active comparison arm

The active comparison sample for the TaSCS trial is a psychiatric nurse-led, centralised model of out-patient specialist mental health care augmented by community outreach by lay workers as part of the Butajira SMD study. There are 57 psychiatric nurse-led units across Ethiopia providing the lion’s share of specialist mental health care in the country [37]. Psychiatric nurse-led clinics constitute the only model of mental health care available in rural areas in Ethiopia. The comparison arm of the TaSCS trial can be considered to be an enhanced version of specialist mental health care, in that community outreach is provided. Evaluation of the longitudinal illness course of patients in the Butajira SMD study showed improved outcomes for those who engaged with the service compared to those who did not engage [2].

The Butajira hospital psychiatric nurses are able to prescribe psychotropic medication (including depot antipsychotic medication), monitor and intervene against side effects, diagnose co-morbid psychiatric conditions and provide simple psychosocial interventions. Follow up will be arranged on the basis of need, but at least a face-to-face assessment every three months. Consultation with project psychiatrists or referral for in-patient psychiatric care (in Addis Ababa) will be as indicated.

The psychiatric nurses will receive 2 days of refresher training in order to familiarise them with the WHO’s evidence-based guidelines for management of mental disorders (mhGAP-IG). They will also receive refresher training on the management of SMD in pregnant and breastfeeding women.

### Fidelity

The competence of the PHC workers to deliver mental health care will be evaluated through pre- and post-training assessments of knowledge and attitudes [45] towards mental health, post-training evaluation of clinical skills [46] and structured supervision reports from the project psychiatric nurses. The fidelity of the task shared mental health care to the mhGAP intervention packages will be measured through structured evaluation of clinical follow-up forms by independent psychiatrists, including prescribing, risk assessment, psychoeducation and symptom review. Medication is being supplied by the trial, but a record will be kept of any interruptions to supply.

The fidelity of the active comparison specialist mental health care model to evidence-based mental health care will be measured through structured evaluation of clinical follow-up forms by independent psychiatrists, as for the intervention arm.

### Outcomes

The trial outcomes are summarised in Table 2.

**Table 2 Tab2:** Summary of outcomes measures for the Task Sharing for the Care of Severe Mental Disorders in a Low-income Country (TaSCS) trial

	Outcome	Measure	Timing
Primary outcome			
1	SMD symptom severity	BPRS-E	Baseline, 12* and 18 months
Secondary outcomes			
1.	Functional impairment^±^	WHODAS 2.0 (12-item)	Baseline, 12 and 18 months
		Local functioning scale	Baseline, 12 and 18 months
2.	Relapse of mental disorder	LCS	Baseline, 12 and 18 months
3.	Service use costs	CSRI	Baseline, 12 and 18 months
4.	Satisfaction with mental health care	Mental health service satisfaction scale (MHSSS)	Baseline, 12 and 18 months
		Qualitative in-depth interviews	From 6 months post-randomisation
5.	Nutritional status	Body Mass Index	Baseline, 12 and 18 months
6.	Service use for physical health conditions	CSRI	Baseline, 12 and 18 months
7.	Medication side effects	ASC	Baseline, 12 and 18 months
8	Patient engagement and adherence	Medication Adherence Measure Clinic attendance	Baseline, 12 and 18 months
9.	Perceived stigma	ISMI	Baseline, 12 and 18 months
10.	Restraint^±^	Proportion chained, restrained or confined in last month	Baseline, 12 and 18 months
11.	Quality of care	Document review	Monthly for 3 months, 6, 12 and 18 months
13.	Adverse events (AEs)	LCS and project reporting mechanisms for AEs	Continuous for serious AEs 6-monthly for other AEs
Mediating variable			
1.	Therapeutic alliance	HAQ	Baseline, 12 and 18 months
Caregiver outcomes			
1.	Perceived stigma	FIS	Baseline, 12 and 18 months
2.	Caregiver burden	FIS	Baseline, 12 and 18 months
3.	Time burden of caring and opportunity costs	CSRI	Baseline, 12 and 18 months
Potential confounding variables			
1.	Sociodemographic characteristics	Structured self-report of age, sex and marital status	Baseline
2.	Socio-economic status	Structured self-report of educational level, occupational status, food insecurity and family size	Baseline
3.	Alcohol use disorder	FAST	Baseline
4.	Khat use disorder	CIDI substance use module	Baseline
5.	Medical co-morbidity or physical disability	Structured self-report	Baseline

* Primary outcome; ^±^ proxy version also administered to caregivers. BPRS-E, Brief Psychiatric Rating Scale, expanded version [6, 60]; WHODAS 2.0, World Health Organisation Disability Assessment Schedule, Version 2.0 [61]; LCS, Life Chart Schedule [62]; CSRI, Client Service Receipt Inventory [63, 64]; ASC, Antipsychotic Side Effect Checklist [65], Medication Adherence Measure [66]; ISMI, Internalised Stigma of Mental Illness [67]; HAQ, Helping Alliance Questionnaire [68]; FIS, Family Interview Schedule [69]; FAST, Fast Alcohol Screening Test [70]; CIDI, Composite International Diagnostic Interview [33]

#### Primary outcome

The primary outcome is non-inferior symptom level, defined as no more than a six-point higher mean score on the BPRS-E [47]. The BPRS-E is a 24-item, clinician-rated scale that was originally developed for detection of symptom change in persons with persistent SMD [47]. Each item is rated on a scale from 1 to 7 (1 = not present; 2 = very mild; 3 = mild; 4 = moderate; 5 = moderately severe; 6 = severe and 7 = extremely severe). The maximum total score is 168. The BRPS-E focuses on symptoms of psychosis but also has items covering the symptom domains of somatic concerns, anxiety, depression and mania. The total BPRS-E score is sensitive to change in treated in-patient populations of persons with persistent SMD, including those with diagnoses of schizophrenia, bipolar disorder and major depressive disorder [48]. The BPRS-E has also been used in treatment trials with out-patient populations of persons with SMD [49, 50] and has been used in Ethiopia previously [51]. The factor structure and sensitivity to change of the BPRS-E has been shown not to vary significantly across diagnostic groups [48]. Inter-rater and test-retest reliability, as well as internal consistency, have been shown to be high [52].

The non-inferiority margin for the primary outcome needs to be defined in relation the minimal clinically important difference (MCID) [53]. Previous studies have defined clinically significant change in score on the BPRS-E in different ways. Using a statistical approach, the ‘reliable change index’ [54] for change in BPRS-E score from beginning to end of an in-patient admission in persons with SMD equated to 18 points [55]. However, change in symptoms in a person with acute psychosis receiving in-patient care is likely to be larger than the MCID and not applicable to the out-patient sample of people with SMD to be included within this sample. In a study looking at change in symptoms in response to a psychological intervention for an out-patient sample of people with chronically symptomatic schizophrenia, a mean change of 7.9 points on the BPRS-E was considered clinically important [49]. A mean change of 7.9 points equates to a standardised effect size of around 0.50, which we take to be the MCID. In line with recommendations for non-inferiority trials, the non-inferiority margin for this trial will be 75 % of the presumed MCID, that is, a six-point difference in mean BPRS-E scores between arms of the trial [53, 56]. A six-point difference on the BPRS-E equates to a standardised effect size of 0.4.

#### Secondary outcomes

See Table 2.

A wide range of secondary outcomes are being assessed in view of the importance of exploring the full range of possible harms when conducting a non-inferiority trial. The secondary outcomes are functional impairment, relapse of SMD, service use costs, satisfaction with mental health care, nutritional status, service use for physical health conditions, disengagement from care, non-adherence with medication, experience of side effects, perceived stigma, experience of being restrained, quality of care and adverse events. Caregiver outcomes are perceived stigma, family burden, time burden and opportunity costs of care giving.

#### Potential confounders

In order to be able to adjust for potential confounding in case of randomly unequal distribution of variables, baseline measurement of the following variables will be carried out: socio-demographic characteristics, socio-economic status, alcohol use disorder, khat use disorder and medical co-morbidity and physical disability. See Table 2.

### Sample size calculation

The following formula was used to calculate the required sample size (n):$$ n={2}^{*}{\left[\sigma /\Delta \right]}^2\;{\left({Z}_{\alpha }+{Z}_{\beta}\right)}^2, $$

where delta = non-inferiority margin (mean BPRS-E scores of six points), sigma is the standard deviation of the BPRS-E score (estimated standard deviation of 15 [57]), Z_alpha_ is the standardised mean difference for the probability of type 1 error (alpha = 0.05) and Z_beta_ is the standardised mean difference for the probability of type 2 error (beta =0.1 (that is, power of 0.9). Therefore, a sample size of 107 persons per arm of the trial (that is, a total of 214) is required [58]. No published studies from Ethiopia are available to guide us in our estimation of the intra-cluster correlation (ICC) for study subjects receiving treatment from a specific health centre. We therefore estimate the ICC to be 0.01, which is the median ICC from a review of 31 cluster-based interventions in PHC [59]. Given that there are 13 health centres within the three districts covered by the Ethiopia TaSCS trial, the design effect will be 1 + (n-1)*ICC (where n = number of subjects per cluster). Therefore, the design effect = 1 + (17–1)*0.01 = 1.16. Assuming a worst-case scenario of 30 % loss to follow-up, the required sample size = 214 * 1.30 * 1.16 = 323 participants. For equal numbers in each arm of the trial, the total sample size will be 324 (n = 162 in each arm).

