#### Data analysis approach

Data analysis will follow a detailed statistical analysis plan that specifies all planned analyses. Data analysis will take place using Stata Version 13 (Stata Corporation, College Station, Texas, USA) under the direction of the trial statisticians. All analyses will be masked to study arm until the analysis is finalized and approved by all investigators. Descriptive analyses will include frequency distributions and measures of central tendency and dispersion, as appropriate, with 95 % confidence intervals. Bivariable comparisons will employ χ^2^, Fisher’s exact, Student’s t- or rank-sum tests, as appropriate. All statistical tests will be one-sided at α = 0.05, as we are testing a hypothesis of non-inferiority and not superiority or equivalence.

Analysis will be by intention-to-treat, that is, on the basis of the group to which the participant is allocated randomly at the beginning of the trial. Intention-to-treat has the potential to lead to false acceptance of the hypothesis of non-inferiority in the presence of a true difference if there is a large cross-over from the primary care to the psychiatric nurse service [60]. Therefore, the intention-to-treat analysis will be presented together with the percentage of participants who deviate from the protocol in the following ways: (1) cross-over protocol deviation which is indicated by the percentage who attend for more than two consecutive visits at the service they were not randomised to receive, unless they were referred to that service, and (2) disengagement from care protocol deviation, which is the percentage who miss more than 50 % of their scheduled health facility appointments (not attending within 2 weeks of the appointment date). Per protocol analyses will also be conducted, and the findings presented as a sensitivity analysis. Account will be taken of clustering at the level of the health facility.

Analysis will be carried out on the complete data set at 12 and 18 months. For the primary outcome time-point of 12 months, it would not be appropriate to carry forward the last observation to replace missing data as this would have taken place at the baseline of the study and could, therefore, increase the chance of non-inferiority even in the presence of a difference between the allocated services.

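### The 30% loss allowance is applied as × 1.30 instead of ÷ 0.70, so 324 participants give about 87.5% power, not 90%, at the stated worst-case loss

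*Protocol article*

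**What the plan says.** The Sample size calculation section of the protocol article sets out these inputs:

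- Margin: "delta = non-inferiority margin (mean BPRS-E scores of six points"
- Spread: "sigma is the standard deviation of the BPRS-E score (estimated standard deviation of 15"
- Type I error: "the probability of type 1 error (alpha = 0.05". The Data analysis approach section settles the direction: "All statistical tests will be one-sided at α = 0.05"
- Type II error: "beta =0.1 (that is, power of 0.9"

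These give 107 per arm, 214 in total. The section then takes an ICC of 0.01 with 17 people per health centre, for a design effect of 1.16, and assumes a worst case of 30% loss to follow-up. The two allowances are combined as "the required sample size = 214 * 1.30 * 1.16 = 323 participants". The conclusion is "For equal numbers in each arm of the trial, the total sample size will be 324 (n = 162 in each arm").

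Under Data analysis approach, the 12-month analysis uses the complete data set and last observation carried forward is rejected. Multiple imputation is planned only if more than 15% of primary outcome scores are missing, and then as an exploratory analysis.

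**The concern.** A loss rate is a fraction of those randomised. To finish with n after losing a fraction d, one must start with n / (1 − d). Starting with n × (1 + d) always leaves too few: here 1.30 × 0.70 = 0.91, so 9% of the required number is missing at exactly the loss the plan says it protects against.

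The primary analysis does not make up the loss, because participants without a 12-month score do not enter it. The number recruited therefore has to carry the whole allowance.

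What is at stake is the chance of showing non-inferiority when the two services are truly equivalent. Lower power makes an inconclusive result more likely. Readers and the DSMB would also take 30% loss to be tolerable at 90% power when it is not.

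**Working it through.** **Inputs** (Sample size calculation section unless noted): SD 15; margin 6, with a true difference of 0 implied by the formula; alpha 0.05, one-sided (Data analysis approach); power 0.90; equal arms; design effect 1 + (17 − 1) × 0.01 = 1.16; loss 30%.

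**1. Reproduce the plan's figures.**

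- n per arm = 2 × (15/6)² × (1.645 + 1.282)² = 107.05, which matches the stated 107 (214 in total). One-sided 0.025 would give 132 per arm, so the plan did use one-sided 0.05.
- 214 × 1.30 × 1.16 = 322.7, hence 323, then 324. The printed total is reproduced only with × 1.30.

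**2. Loss that × 1.30 covers.**

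- 1 − 1/1.30 = 23.1%.
- After rounding up to 324: 1 − 248.2/324 = 23.4%, where 248.2 = 214 × 1.16 is the number needed for analysis.

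**3. Power of 324 at 30% loss.**

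- Analysed: 324 × 0.70 = 226.8, about 21 fewer than 248.2 (9% short).
- Effective n per arm: 226.8 / 1.16 / 2 = 97.8, against 107.
- Standard error of the difference: 15 × √(2/97.76) = 2.146.
- Power = Φ(6/2.146 − 1.645) = Φ(1.15) = 87.5% (87.3% with the t distribution).

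**4. Correct inflation.**

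- 214 × 1.16 / 0.70 = 354.6, so 355, or 356 for equal arms. That is 32 more than 324, about 10%.
- Check: 356 × 0.70 = 249.2 analysed, which gives 90.1% power.

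**5. Power of 324 by loss rate**

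| Loss | Analysed | Power, design effect fixed at 1.16 | Power, design effect recomputed from analysed cluster size |
|---|---|---|---|
| 20% | 259.2 | 91.1% | 90.4% |
| 23% | 249.5 | 90.1% | 89.6% |
| 30% | 226.8 | 87.5% | 87.4% |

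The last column uses design effect = 1 + (analysed/13 − 1) × 0.01, with the 13 health centres named in the protocol. On that basis 90% power holds up to about 21.7% loss.

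**The case against.** The slip itself is not in dispute. The case on the other side is about its importance and about how firm the 87.5% is.

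- **Size.** The shortfall is 2.5 power points, and only in the case the plan itself calls the worst. At 20% loss the same inputs give 91%. No participant, analysis, margin or decision rule changes, and the error cannot create a false claim of non-inferiority. All of this stands.
- **Baseline adjustment.** The Analysis of primary outcome section specifies linear regression adjusting for baseline symptom severity, and the sample size formula takes no credit for it. If 15 is the unadjusted SD, variance shrinks by 1 − r², where r is the baseline-to-12-month correlation. At 30% loss, r of about 0.29 restores 90%; r = 0.4 gives 92.0% and r = 0.5 gives 94.3%. The protocol gives no correlation, so these values are assumptions. They show that the design may do better than 87.5%, but they do not make the printed line correct.
- **Clustering in one arm.** The control arm attends a single hospital clinic, so health-centre clustering of care might be counted only in the intervention arm. With 113.4/13 = 8.7 analysed per centre, that arm's design effect is 1.08, and 324 with 30% loss gives 90.5%. Without any design effect the figure is 91.4%. These are other calculations from the one in the plan, which applies 1.16 to the whole sample.
- **Cluster size.** A design effect of 1.24, from 324/13 = 24.9 randomised per centre, would lower power at 30% loss to about 85.6%. That sets a randomised cluster size against an analysed sample. At 30% loss the analysed size is 226.8/13 = 17.4, so 1.16 is about right there. The 85.6% should not be used to enlarge the point.
- **The 23% limit.** It holds with the design effect fixed at 1.16. If the design effect follows the analysed cluster size, the limit is nearer 22%. This stands and belongs in the restated text.

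**Conclusion.** The calculation is wrong as printed. By the plan's own formula and inputs, 324 participants give 87.5% power at 30% loss, not 90%, and 90% power holds only up to about 23% loss (about 22% if the design effect is recomputed). The total that meets the stated aim is 355, or 356 for equal arms.

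This rests on an SD of 15, a true difference of zero, a design effect of 1.16 applied to both arms, no credit for baseline adjustment, and a primary analysis limited to participants with a 12-month score. A baseline correlation of about 0.29 or more would remove the shortfall, but the plan neither states nor uses one. The error is certain and should be corrected because the power statement is relied on; its practical effect is modest.

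**What to change.** Keep the total at 324. In the Sample size calculation section, replace the last step with 214 × 1.16 / (1 − loss) and restate what 324 delivers. For example: *With 324 randomised, power for an unadjusted comparison at one-sided alpha 0.05 is 87.5% at 30% loss to follow-up; 90% power holds for loss up to about 23% with the design effect held at 1.16.* If the design effect is itself revised, take both figures from the fully corrected formula. If the sponsor wishes to rely on the baseline adjustment, the assumed correlation and its source should be stated beside the result.

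The cost is one corrected line and a slightly less favourable power statement. No extra participants are needed. The article reports recruitment as ongoing, so the correction can be made before results are known.
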